### Outcomes

The primary outcome of this study is optimal PrEP adherence over the 6-month study period, defined as a binary outcome (optimal vs suboptimal adherence) and assessed separately for event-driven and daily PrEP users. Adherence will be measured primarily using EMA data collected through the PLP Camp platform version 2.0, whereas survey data collected at baseline and follow-up visits will be used to support interpretation and cross-validation of adherence-related measures.

For daily PrEP users, each PLP Camp check-in will record whether the participant has taken 1 PrEP pill within the preceding 24 hours. Adherence will be calculated as the proportion of days with reported pill intake out of all days under observation during each monitoring period. In constructing this outcome, days without a submitted PLP Camp check-in will be operationally treated as days without reported pill intake. Daily users with adherence of 80% or higher during the relevant monitoring period will be classified as having optimal adherence, whereas those with adherence below 80% will be classified as having suboptimal adherence [4,8,35].

For event-driven PrEP users, each PLP Camp check-in will capture sexual behavior and PrEP use occurring within the reporting interval, defined as the time since the previous check-in up to a maximum of 72 hours. Adherence will be assessed at the level of reported sexual encounters according to the standard 2-1-1 regimen. A reported sexual encounter will be classified as adherent if the participant reports taking 2 PrEP pills 2 to 24 hours before sex, 1 pill 24 hours after the initial dose, and 1 additional pill 48 hours after the initial dose. Event-driven users will be classified as having optimal adherence if all reported sexual encounters during the relevant monitoring period meet these dosing requirements; otherwise, they will be classified as having suboptimal adherence. Intervals without a submitted PLP Camp check-in will be treated as intervals without a reported sexual encounter, and therefore, event-level adherence will be assessed only for reported sexual encounters.

Secondary outcomes will include platform-related implementation outcomes, namely, effectiveness, acceptability, and feasibility of the PLP Camp platform, as well as individual-level determinants related to PrEP adherence, including PrEP-related knowledge, self-efficacy for maintaining adherence, risk perception of HIV infection and PrEP nonadherence, barriers to and facilitators of adherence, PrEP stigma, and social support. These outcomes will be measured using surveys administered at baseline and follow-up visits.

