### Statistical Analysis

All analyses will follow the intention-to-treat principle, whereby all randomized participants will be analyzed according to their assigned study group regardless of intervention uptake, regimen changes, or follow-up completeness. Baseline characteristics will be summarized by study group using appropriate descriptive statistics.

The primary analysis will assess between-group differences in optimal PrEP adherence over time. As the primary outcome is binary and repeatedly measured, generalized linear mixed-effects logistic regression models will be used, including fixed effects for study group, time, and the group-by-time interaction and a participant-level random intercept to account for within-participant correlation. Prespecified baseline covariates will be included to improve precision and adjust for residual imbalance. Effect estimates will be presented as odds ratios with 95% CIs.

Adherence outcomes will be constructed according to the prespecified regimen-specific definitions described above. For daily PrEP users, days without a recorded PLP Camp check-in during each monitoring period will be operationally treated as days without reported pill intake based on previous literature [36,37]. For event-driven PrEP users, adherence will be assessed only for reported sexual encounters according to the standard 2-1-1 regimen; intervals without a submitted PLP Camp check-in will be treated as intervals without a reported sexual encounter.

Secondary outcomes will be analyzed using mixed-effects models appropriate to outcome type, with fixed effects for study group, time, and the group-by-time interaction and participant-level random effects. All tests will be 2 sided, with statistical significance defined as *P*<.05. Analyses will be conducted using the R software.

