### Missing Data Handling

Missing data are expected to arise primarily from incomplete or absent EMA check-ins and missed follow-up assessments. Prespecified regimen-specific rules used to derive adherence outcomes will be treated as part of the outcome definition rather than as missing data imputation. In the primary analysis, generalized linear mixed-effects models will use all available observed repeated adherence outcomes without requiring complete data at every follow-up time point. This likelihood-based approach allows participants with partially observed follow-up data to contribute to the analysis and is consistent with the intention-to-treat principle under the assumption that missingness depends on observed data.

Sensitivity analyses will be conducted to assess the robustness of the findings to alternative assumptions regarding missing data. First, multiple imputation by chained equations will be applied to missing interval-level adherence outcomes and missing covariate data. The imputation models will include study group, time, prior adherence, baseline characteristics, and other variables associated with adherence or missingness. Estimates from the imputed datasets will be combined using the Rubin rules. Second, complete-case analyses will be performed for comparison. Third, additional sensitivity analyses will examine less favorable assumptions for missing adherence outcomes to assess the extent to which the main conclusions depend on departures from the primary missing data assumption.

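### For daily users a missed check-in is scored as a missed pill and then counted as observed data, so the listed sensitivity analyses do not clearly test the rule

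*Protocol article*

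**What the plan says.** Outcomes defines daily adherence as "the proportion of days with reported pill intake out of all days under observation during each monitoring period". It adds that "days without a submitted PLP Camp check-in will be operationally treated as days without reported pill intake", and sets the cut: "Daily users with adherence of 80% or higher during the relevant monitoring period will be classified as having optimal adherence". Statistical Analysis repeats the rule and supports it by citation: "days without a recorded PLP Camp check-in during each monitoring period will be operationally treated as days without reported pill intake based on previous literature".

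Missing Data Handling opens with "Missing data are expected to arise primarily from incomplete or absent EMA check-ins and missed follow-up assessments". It continues: "Prespecified regimen-specific rules used to derive adherence outcomes will be treated as part of the outcome definition rather than as missing data imputation". The primary mixed model then relies on missingness depending on observed data. Three kinds of sensitivity analysis follow:

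- imputation: "multiple imputation by chained equations will be applied to missing interval-level adherence outcomes and missing covariate data";
- complete-case analysis;
- a third group, in which "additional sensitivity analyses will examine less favorable assumptions for missing adherence outcomes".

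Under Real-Time Monitoring, both arms use the platform and daily users get an SMS prompt every 24 hours. Under Precision Intervention Component, only the intervention arm has the education, chatbot, forum, reminder and consultation modules on that platform. Surveys support interpretation and cross-validation (Outcomes).

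**The concern.** A daily user's recorded adherence mixes two behaviors: taking the pill and logging it. Someone who takes every pill but logs 79% of days is classed as suboptimal. The intervention gives one arm more reasons to open the application that collects the outcome, so logging could rise there without any change in pill-taking. The analysis would read that rise as adherence.

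A sensitivity analysis is the natural safeguard, but Missing Data Handling pulls two ways. Absent check-ins are named as a main source of missing data, while the rule that scores them is declared not to be missing-data handling. If the rule stays in force in the sensitivity analyses, an unlogged day is an observed zero, and neither imputation nor complete-case analysis reaches it. At stake is whether a positive daily-user result could be told apart from a logging effect.

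**Working it through.** The plan gives no figure for the effect of this rule, so there is none to reproduce.

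**Inputs from the protocol.** 80% cut (Outcomes); 17.5-point design difference for daily users (Sample Size Planning); 55 daily users per arm (Randomization and Blinding); 6 months of use, taken as 180 days.

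**Assumptions, not in the protocol.** The check-in rates, the true pill-taking rate and the spread of check-in between people.

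**Step 1: check-in rate needed to pass.** Recorded adherence = true adherence × check-in rate, so the rate needed is 0.80 / true adherence.

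| True adherence | Check-in needed |
|---|---|
| 100% | 0.80/1.00 = 80.0% |
| 95% | 0.80/0.95 = 84.2% |
| 90% | 0.80/0.90 = 88.9% |
| 85% | 0.80/0.85 = 94.1% |

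**Step 2: one 30-day period.** Passing needs 0.80 × 30 = 24 recorded days. With X ~ Bin(30, 0.95 × check-in rate), P(X ≥ 24) is 0.999, 0.866, 0.647, 0.396 and 0.198 at check-in rates of 100%, 90%, 85%, 80% and 75%. Pill-taking is 95% throughout.

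**Step 3: same pill-taking in both arms, different check-in.** Each person's check-in probability is drawn from Beta(km, k(1−m)), with mean m and concentration k; a smaller k means more spread. Recorded days are Bin(180, 0.95 × check-in), and passing needs 144. With k = 8, the share classed as optimal is 46%, 62% and 78% at m = 80%, 85% and 90%. The spurious difference for 80% against 85% depends on k:

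| k | Difference (points) |
|---|---|
| 2 | about 10 |
| 4 | about 13 |
| 8 | about 16 |
| 20 | about 23 |

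With 30-day periods in place of 180 days, it is about 12, 14 and 18 points at k = 5, 8 and 20. Far below the cut the effect is small: 50% against 55% gives about 2 points at k = 8 and 5 at k = 2 (180 days).

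**Step 4: a second set of assumptions.** True adherence varies around a mean of 90%, and k = 5 for check-in. Then 80% against 85% gives about 11 points and 80% against 90% about 24. In a simple two-sided 5% comparison with 55 per arm, the chance of a significant result favoring the better-logging arm is about 22% and 70%, although pill-taking is identical. The planned mixed model was not simulated.

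**Step 5: do the listed analyses reach the rule?** Under the rule, every daily-user period under observation has a value.

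- *Imputation:* acts on missing outcomes, and the text does not say that unlogged days become missing.
- *Complete-case analysis:* selects on the same derived outcomes.
- *Less favorable assumptions:* a day is either intake or non-intake, and an unlogged day already has the worse value.

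**The case against.** The rule is disclosed, prespecified and cited, and scoring non-report as non-intake is a legitimate conservative choice. That stands, and is why the primary rule need not change.

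Differential check-in is an assumption. Both arms get the same SMS prompt. Reminders and consultation are for high-risk users and the forum for medium-risk users, so those near the 80% cut mainly see education and the chatbot. Education sent one-to-one by WeChat need not lead to a check-in. All of this is correct: the protocol shows an opportunity for imbalance, not an imbalance.

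The surveys are a second source, and platform use is collected as a feasibility measure. Both help. However, no rule covers disagreement between survey and platform, and the survey item described under Data Collection is framed around sexual encounters rather than daily pills.

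A reader might infer that nothing is left to impute and that the sensitivity analyses would simply return the primary data. The protocol does not support this. The imputation also covers covariates. Days under observation are not defined, so periods after withdrawal may be missing. The mention of interval-level outcomes could be read as reopening unsubmitted intervals.

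A reader might also infer that the event-driven sensitivity analyses do nothing. That is not established either: a period with no reported encounter may have no defined outcome, and the event-driven rule works the other way, since an unreported encounter cannot count against the user.

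**Conclusion.** The point holds in a limited form. For daily users, non-reporting is scored as non-intake and treated as observed. As worded, imputation and complete-case analysis do not clearly test that choice, and less favorable assumptions cannot.

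The possible size is material: about 10 to 23 points of spurious difference for a 5-point gap in mean check-in near the cut, against 17.5 points planned. This rests on assumed check-in rates of 80% and 85%, 95% pill-taking in both arms, one 180-day classification and k between 2 and 20. The bias between arms vanishes if check-in is equal and is small if check-in is well below the cut in both arms. The daily stratum is 110 of the 430 planned participants. The protocol does not show that a positive result would be an artifact; it leaves no clear means of ruling that out.

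**What to change.** Keep the primary rule. In Missing Data Handling, state that for daily users the sensitivity analyses recode unsubmitted days as missing before the outcome is derived, and then:

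1. analyse submitted days only;
2. multiply impute at day level, with study arm in the imputation model;
3. apply arm-specific shifts to the imputed values, to show how large a departure would change the conclusion.

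Report check-in rates by arm beside the primary daily-user result. For event-driven users, state that unsubmitted intervals are likewise treated as missing, rather than encounter-free, in the sensitivity analyses.

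The cost is revised wording and extra programming; no new data are needed. The downside is that the daily-user result may look less robust. The protocol reports that the intervention is ongoing and the data unviewed, so the change can still be made without knowledge of results.

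### Event-driven users: an interval with no check-in is scored as having no encounter, so silence inflates optimal adherence and can distort the arm comparison in either direction

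*Protocol article*

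**What the plan says.** The Outcomes section of the protocol article scores event-driven users on reported encounters only: "Event-driven users will be classified as having optimal adherence if all reported sexual encounters during the relevant monitoring period meet these dosing requirements"; everyone else is suboptimal. On silence it says: "Intervals without a submitted PLP Camp check-in will be treated as intervals without a reported sexual encounter". Statistical Analysis repeats this for the primary analysis: "For event-driven PrEP users, adherence will be assessed only for reported sexual encounters according to the standard 2-1-1 regimen". It also states that "all randomized participants will be analyzed according to their assigned study group regardless of intervention uptake, regimen changes, or follow-up completeness". Neither section sets a minimum number of check-ins or encounters, or says what a period with no reported encounter becomes.

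For daily users the rule runs the other way: "days without a submitted PLP Camp check-in will be operationally treated as days without reported pill intake". For the platform's risk classification, Real-Time Monitoring uses a third rule: a participant who reports nothing keeps the last reported risk level.

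Missing Data Handling opens with "Missing data are expected to arise primarily from incomplete or absent EMA check-ins and missed follow-up assessments", and then says "Prespecified regimen-specific rules used to derive adherence outcomes will be treated as part of the outcome definition rather than as missing data imputation". Among the sensitivity analyses, "multiple imputation by chained equations will be applied to missing interval-level adherence outcomes and missing covariate data"; complete-case analyses and unspecified less favourable assumptions follow. Surveys only support interpretation and cross-validation.

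**The concern.** The rule does not separate two situations: a participant who checked in and reported no sex, and a participant who did not check in. In the second, any non-adherent encounter in the interval disappears. A check-in covers at most the preceding 72 hours, so on that definition a later one does not recover it. Since optimal means that no reported encounter failed, each lost failing encounter can only move the classification towards optimal. A wholly silent period contains no failing encounter, and with only two categories the wording places it in optimal.

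Event-driven users are 320 of the planned 430 participants (74%). If check-in behaviour differs between arms, the primary comparison in this stratum mixes reporting with adherence. Such a difference is plausible: the trial is open label and only the intervention arm has the chatbot, forum, reminders and consultation. The article's limitations paragraph itself lists behaviour recording among the functions that depend on engagement.

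**Working it through.** **Inputs from Sample Size Planning and Randomization.** Control optimal 45%; detectable difference 17.5 points, so intervention 62.5%; 320 event-driven users, 160 per arm; 20% loss; 80% power. Statistical Analysis specifies two-sided tests at 0.05.

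**Reproducing the plan's figure.** Two proportions, pooled variance under the null, mean proportion 0.5375:

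n = [1.96·√(2·0.5375·0.4625) + 0.84·√(0.45·0.55 + 0.625·0.375)]² / 0.175² ≈ 127 per arm, 254 in total; 254/0.8 ≈ 318.

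This matches 320 with a two-sided alpha. (The printed Z of 1.64 would give 250, which is a separate matter.) Power is 81% at the 128 per arm left after 20% loss and 88% at all 160. When silence is scored rather than missing, nobody is lost, so 160 per arm and 88% is the reference below.

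**Assumptions.** The article gives no check-in rate. The 20% is defined as not completing follow-up questionnaires, so it illustrates silence and does not bound it. Power figures are for a simple two-proportion comparison in one period, not for the mixed model.

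**A. Wholly silent participants, literal reading.** With silent share s and true proportion p, recorded optimal = s + (1 − s)p. A true 45% is recorded as 50.5%, 56.0% or 61.5% for s = 10%, 20% or 30%.

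| True (control / intervention) | Silent (control / intervention) | Recorded (control / intervention) | Difference, points | P(reject), 160 per arm |
|---|---|---|---|---|
| 45 / 62.5 | 0 / 0 | 45 / 62.5 | 17.5 | 0.88 |
| 45 / 62.5 | 20 / 20 | 56 / 70 | 14.0 | 0.74 |
| 45 / 62.5 | 30 / 10 | 61.5 / 66.25 | 4.75 | 0.14 |
| 45 / 62.5 | 10 / 30 | 50.5 / 73.75 | 23.25 | 0.99 |
| 45 / 45 | 10 / 30 | 50.5 / 61.5 | +11.0 | 0.51 |
| 45 / 45 | 30 / 10 | 61.5 / 50.5 | −11.0 | 0.51 |

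Scoring the same silence as suboptimal, as for daily users, gives (1 − s)p. The third row becomes 0.9·62.5 − 0.7·45 = 24.75 points, and the fourth 0.7·62.5 − 0.9·45 = 3.25. The coding of silence alone moves the result by 20 points.

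**B. Selective silence, almost independent of the zero-report question.** Assume k encounters per period, each adherent with probability q where q^k = 0.45, and failing encounters reported with probability r. Recorded optimal = (1 − (1 − q)r)^k. For k = 8, q = 0.905: r = 0.7 gives 57.7% and r = 0.5 gives 67.8%. For r = 0.7, k = 4 to 12 gives 58.2% to 57.5%. With no true effect, r = 0.9 in control and 0.7 in intervention gives 48.9% against 57.7%, about 9 points (rejection 0.35); swapping r reverses the sign.

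**C. Both readings of a zero-report period.** Assume encounters per period are Poisson with mean 4, q ~ Beta(3.4, 0.6) (mean 0.85), coverage c and drop-out d, with no true effect. Let g(m) = E[exp(−m(1 − q))].

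- Truth: g(4) = 63.9%.
- Literal: d + (1 − d)·g(4c). For d = 20%, c = 80%: 0.2 + 0.8·0.686 = 74.9%. For d = 10%, c = 90%: 0.1 + 0.9·0.662 = 69.6%. The gap is just over 5 points.
- Zero-report periods not evaluable: [g(4c) − exp(−4c)] / [1 − exp(−4c)], giving 67.3% and 65.2%, a gap of about 2 points. The truth among those with at least one encounter is 63.3%.

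**The case against.** The strongest objection is that no sentence says a period with no reported encounter is optimal. Adherence is assessed only on reported encounters, and the mixed model is said to use the outcomes that are observed, so such a period could be meant as not evaluable. A reader might therefore state as fact that drop-outs are counted as successes, and the documents do not support that. It is what the two-category wording yields, not something it says. The objection stands as a limit on size: calculation A depends on that reading, and in C the gap falls from just over 5 points to about 2. It does not remove the defect, because failing encounters in unreported intervals are lost under either reading.

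A reader might also infer that the intervention arm will check in more and so be penalised. The documents do not fix that direction. SMS prompts every 72 hours and WeChat reminders for inactive users go to both arms, and raising check-in rates is not a stated aim.

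The plan does foresee multiple imputation, complete-case and less favourable analyses, survey cross-validation, and overestimation from self-report. These address missing outcomes or aid interpretation. Because the rule is placed in the outcome definition, silent intervals are not missing unless they are recoded, and the text does not say they are. The primary estimate is unchanged in any case.

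Two lesser points are fair. The all-or-nothing criterion follows the earlier cohort's definition of strict 2-1-1 use, so it is not itself an error. The opposite rules for the two regimens matter less because the regimens are assessed separately.

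**Conclusion.** The concern holds. The protocol fixes a rule that scores non-reporting as absence of an encounter, in the stratum that makes up 74% of the planned sample, while naming absent check-ins as a leading source of missing data. The proportion optimal is biased upward. The bias in the between-arm effect has no fixed sign: equal silence attenuates it, and unequal silence can inflate, mask or reverse it.

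The size depends on silence rates that the documents do not give. For 10% to 30% silence on the literal reading, it runs from a loss of 3.5 points off the planned 17.5 (equal 20% silence) to a spurious 11 points under no effect, or a true 17.5 reduced to 4.75. If zero-report periods are not evaluable, the effect is smaller but remains. This should be settled before the data are viewed.

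**What to change.** In Outcomes, Statistical Analysis and Missing Data Handling:

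1. Count an event-driven interval as having no encounter only when a submitted check-in says so. Treat an interval with no check-in as missing.
2. Do not class a period as optimal if it has no check-ins, or coverage below a minimum fixed before the data are viewed. Set it to missing for the mixed model and multiple imputation.
3. State how a period of confirmed no sex is handled.
4. Say explicitly that silent event-driven intervals enter the multiple imputation and the less favourable analyses. Silence may follow non-adherent sex, so missing at random is doubtful, and the mixed model and imputation alone are not enough.
5. Report check-in coverage and the number of reported encounters by arm.

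An encounter-level analysis (proportion of encounters adherent) would be useful support but is optional.

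The cost is revised wording and modest programming. The article says that the research team has not viewed the data, so the change can still be prespecified. Some participant-periods become non-evaluable, with slightly lower precision.
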